### Blinding, data collection, randomization and record-keeping

This is a single-blinded (participant) study. Patient data, intraoperative and postoperative measurements, fluid balance, respiratory parameters, laboratory results and clinical status (Sequential Organ Failure Assessment (SOFA) score) will be collected onto Case Report Forms (CRF). CRF and the patient evaluation chart will not be assessed in front of the patient.

Participants will be randomized to the SG or CG in a ratio of 1:1. Randomization will be carried out by a computer-generated blocked randomization list with 10 blocks of four patients per block. Allocation will be stored in sealed, opaque and numbered envelopes. Participants will be included and allocated in numerical order.

All original records (CRF and relevant correspondence) will be archived and secured for 15 years, and then destroyed according to the hospital standards concerning destruction of confidential information.

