### Time course of the study

#### Preoperative assessment and admission

During standard institutional preoperative assessment, the patient’s eligibility for radical cystectomy and urinary diversion will be evaluated. Medical history, laboratory and chest X-ray or computed tomography (CT) scan, 12-lead electrocardiogram (ECG), ASA physical status, BMI, Respiratory Failure Risk Index (RFRI), nutritional risk screening (NRS 2002 tool) and, if required (in case of history of smoking or coronary artery disease), results of spirometry, echocardiography and ergometry will be recorded. Participants fulfilling the inclusion criteria will be asked for their signed informed consent.

After admission to the Department of Urology (on the day before surgery) a central venous catheter will be placed, a blood sample will be taken from included patients for baseline levels of PCT (T_0_), a chest X-ray will be performed and, if there are no exclusion criteria, patients will be randomized into one of the study groups. Patients will be given oral carbohydrate loading (maltodextrin) 12, 8 and 2 h before surgery, 1000 mL of crystalloid solution will be given and antimicrobial prophylaxis will be introduced using ciprofloxacin and metronidazole 30 min before surgical incision. Antimicrobial prophylaxis will be continued for 72 h (2 × 400 mg ciprofloxacin and 3 × 500 mg metronidazole per day). Deep vein thrombosis prophylaxis will be carried out using low-molecular-weight heparin (LMWH).

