#### Intraoperative care

Before induction of anesthesia an epidural catheter and an arterial cannula will be inserted for invasive arterial blood pressure monitoring and blood gas sampling.

Immediately after induction of anesthesia and orotracheal intubation, once a steady state has been reached (Table 2), all patients will be submitted to an ARM using the sustained airway pressure by the CPAP method, applying 30 cmH_2_O PEEP for 30 s. After ARM, PEEP will be set to 6 cmH_2_O in the CG (“standard PEEP”) and LPV (TV = 6 mL/Kg IBW, FiO_2_ = 0.5) will be performed. In the SG (“optimal PEEP”) PEEP will be determined during a Cstat-directed decremental PEEP titration procedure. During surgery ARM will be repeated and arterial and central venous blood gas samples (ABGs, CVBGs) will be evaluated every 60 min. In case of decreased oxygen saturation (SpO_2_ < 94%) rescue ARM will be performed using a FiO_2_ of 1.0. PCT levels will be measured 2, 6, 12, 24, 48 and 72 h after surgical incision.

**Table 2 Tab2:** Steady state after induction of anesthesia

	Parameter	Value
Hemodynamics	Mean arterial pressure	65 mmHg < MAP < 90 mmHg
	Heart rate	50/min < HR < 100/min
Ventilation	SpO_2_	≥96%
	EtCO_2_	35–40 mmHg
Anesthetics	EtSevo	1.0 MAC

*MAP* mean arterial pressure, *HR* heart rate, *SpO*
_*2*_ peripheral capillary oxygen saturation, *EtCO*
_*2*_ end-tidal carbon dioxide partial pressure, *EtSevo* end-tidal sevoflurane concentration, *MAC* minimal alveolar concentration

Arterial blood pressure, heart rate (HR) and end-tidal carbon dioxide tension (EtCO_2_) will be monitored continuously. Cstat, airway resistance (Raw), Vds/Vt, core temperature and train-of-four relaxometry data will be recorded every 15 min.

During surgery, in cases of hypotension, intravenous norepinephrine will be started to maintain mean arterial pressure above 65 mmHg. For intraoperative fluid management patients will receive 3 mL/Kg/h of balanced crystalloid solution until end of surgery. In cases of bleeding, a 200-mL colloid (hydroxyethyl starch, HES) solution bolus and crystalloid substitution will be given. Packed red blood cell (PRBC) transfusion will be given whenever the attending anesthetist feels it necessary.

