### Study arms and assigned intraoperative interventions

A total number of 40 patients with bladder cancer submitted to general anesthesia and open radical cystectomy and urinary diversion will be enrolled in this study. An equal number of patients will be randomized into the two groups.

Patients randomized into the SG group undergo an alveolar recruitment maneuver using the sustained airway pressure by the CPAP method, applying 30 cmH_2_O PEEP for 30 s followed by a decremental PEEP titration procedure directed by Cstat. During the PEEP titration procedure, PEEP will be decreased from 14 cmH_2_O by 2 cmH_2_O every 4 min, until a final PEEP of 6 cmH_2_O is reached. On each level of PEEP, ABGs will be collected and evaluated. Optimal PEEP is considered as the PEEP value resulting the highest possible Cstat measured by the ventilator. After the PEEP titration procedure, lung-protective mechanical ventilation will be performed using optimal PEEP and low tidal volumes and ARM will be performed every 60 min.

Patients randomized into the CG group will undergo an alveolar recruitment maneuver using the sustained airway pressure by the CPAP method, applying 30 cmH_2_O PEEP for 30 s followed by low-tidal-volume LPV using a PEEP value of 6 cmH_2_O and ARM will be repeated every 60 min.

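### Fixed, published blocks of four leave between about 8% and 33% of allocations determined before the envelope is opened, and randomising on the day before surgery lets the arm be known during care common to both arms

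*Protocol article*

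**What the plan says.** All references are to the Protocol article.

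- **List.** The section on blinding, data collection, randomization and record-keeping says "Randomization will be carried out by a computer-generated blocked randomization list with 10 blocks of four patients per block" and "Participants will be randomized to the SG or CG in a ratio of 1:1". It adds "Allocation will be stored in sealed, opaque and numbered envelopes", with participants taken in number order.
- **Size.** The sample is given as "A total number of 40 patients with bladder cancer submitted to general anesthesia and open radical cystectomy and urinary diversion will be enrolled", and the split between the arms as "An equal number of patients will be randomized into the two groups". Both stand under Study arms and assigned intraoperative interventions.
- **Blinding.** "This is a single-blinded (participant) study".
- **Centres.** Study design names two centres. How the numbered envelopes are divided between them is not described.
- **Time of randomisation.** Under Preoperative assessment and admission, the steps after admission on the day before surgery are a central line, the baseline procalcitonin sample and a chest X-ray. Then, "if there are no exclusion criteria, patients will be randomized into one of the study groups".
- **Time of divergence.** Under Intraoperative care, after intubation and steady state, "all patients will be submitted to an ARM using the sustained airway pressure by the CPAP method". PEEP is fixed in the control group or titrated in the study group only after that maneuver.
- **Analysis set.** Statistics specifies intention to treat.

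**The concern.** Opaque envelopes hide the next card but not the count of cards left in a block. Anyone who knows the block size and the earlier allocations in the block can sometimes name the next arm before the envelope is opened. The article itself discloses the block size. It is dated August 2017, inside a recruitment period planned from October 2016 to March 2018. The staff who ventilate the patient must know the arm, because they either set a fixed PEEP or run a stepwise titration.

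Selective enrolment is the risk. Local staff make a final exclusion check just before randomisation, and some criteria call for judgement, such as severe or uncontrolled asthma. Duration of the trial gives about 100 operations a year over 18 months, or roughly 150 candidates for 40 places, so there is room to choose whom to enrol and when. The definition of pulmonary complications includes auscultation, and no assessor is described as masked. Concealment therefore carries much of the protection against bias.

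Timing is a separate matter. Nothing described between randomisation and the end of the first recruitment maneuver needs the arm to be known. Early allocation exposes preoperative care, epidural placement, induction and steady state to that knowledge. It also means that a patient whose operation is cancelled or changed is already randomised.

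**Working it through.** **Inputs from the article:** block size 4, 10 blocks, 1:1 (two places per arm in each block), 40 patients, two centres. **Assumption, varied below:** what the recruiter knows of earlier allocations. The recruiter is taken to know the block size and each patient's place in the block, which sequential numbering makes possible.

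**1. The plan's own figure.** 10 × 4 = 40, which agrees with the stated total.

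**2. Share determined, all earlier allocations in the block known.** There are C(4,2) = 6 equally likely orders. An allocation is determined once one arm's two places are used.
- Places 1 and 2: never.
- Place 3: when the first two match, in 2 of 6 orders = 1/3.
- Place 4: always.

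Per block: 1/3 + 1 = 1.333. As a share: 1.333/4 = 8/24 = 33.3%. Over ten blocks: 13.3 of 40 expected, and never fewer than 10.

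**3. Best guess, same knowledge** (choose the arm with more places left, toss a coin if equal). The chances of being right at places 1 to 4 are 1/2, 2/3, 2/3 and 1. Their mean is (0.500 + 0.667 + 0.667 + 1)/4 = 17/24 = 70.8%, against 50% for unpredictable allocation.

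**4. One list shared by two centres that exchange nothing.** Let p be the share recruited at one centre.
- Place 4 is determined when the two earlier patients who filled one arm were at the same centre as the fourth: probability p³ + (1−p)³.
- Place 3 is determined when all three patients share a centre and the first two share an arm: [p³ + (1−p)³]/3.

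The sum divided by 4 is [p³ + (1−p)³]/3.

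| Recruitment split | Share determined | Patients of 40 |
|---|---|---|
| 50:50 | 0.250/3 = 8.3% | 3.3 |
| 70:30 | 0.370/3 = 12.3% | 4.9 |
| 90:10 | 0.730/3 = 24.3% | 9.7 |
| 100:0 | 1/3 = 33.3% | 13.3 |

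Enumerating the 50:50 case gives a best-guess rate of 59.9%. If whole blocks are assigned to each centre, the results of steps 2 and 3 apply again.

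**5. Randomly varying blocks.** Simulation, with an observer who knows every past allocation and the set of possible sizes:

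| Block sizes | Certain | Best guess right |
|---|---|---|
| 4 only | 33% | 71% |
| 4, 6 | about 5% | 69% |
| 2, 4, 6 | about 4% | 70% |
| 4, 6, 8 | about 2% | 68% |

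**6. Timing, by reading.** Randomisation falls on the day before surgery. Carbohydrate loading, fluids, antibiotics, epidural, induction, steady state and the first recruitment maneuver are specified alike for both arms. A patient lost in that interval has a baseline procalcitonin value, but none from 2 h after incision onward and no postoperative period in which to assess complications.

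**The case against.** A reader might infer that a third of allocations are known to staff in this trial. The article does not support that. It says that only the participant is blinded. It does not say who holds or opens the envelopes, or that recruiters see every past allocation, least of all the other centre's. One third is a ceiling, and 8% is possible.

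A reader might also add a centre-imbalance problem. With one interleaved list and equal recruitment, the arms would differ by four or more patients within a centre in about 27% of trials. That figure applies only to the shared list, where the determined share is 8% unless the centres exchange allocations. If whole blocks go to each centre, the 33% returns but the imbalance disappears. The layout is not stated, so the two figures should not be combined.

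A count of overnight cancellations is tempting too, but the article gives no cancellation rate and does not say whether such patients are replaced. The loss cannot be sized.

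On scope for selection, consent may be sought before the next envelope can be predicted, and most exclusions are graded or historical facts. On timing, eve-of-surgery randomisation contradicts nothing in the article, and the common care is standardised. When the team learns the arm is not stated; early knowledge is inferred from the time of randomisation.

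These points limit the size of the finding. They do not remove it: the block size is fixed and disclosed, the last exclusion check rests with local staff, and the interval between randomisation and divergence serves no described purpose.

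**Conclusion.** The point holds as a range. Between about 8% (3.3 of 40) and 33% (13.3 of 40) of allocations are determined before the envelope is opened. The lower figure assumes one list shared by two equally recruiting centres with no exchange of information; the upper assumes blocks kept within a centre or all earlier allocations known. A recruiter at the upper end guesses right 71% of the time. All these figures assume that the block size and the place within the block are known. They measure opportunity; nothing in the article shows that selection occurred.

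The timing point is accurate on the text but cannot be quantified: allocation precedes divergence by about a day, so the arm can be known during common care and avoidable post-randomisation losses become possible. Together these justify a change for the remaining patients. They do not invalidate the design.

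**What to change.** For patients not yet randomised:

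1. Randomise by opening the next envelope in the operating room immediately before the arms diverge, that is, after the first recruitment maneuver. Eligibility and consent are settled by then, and few cancellations can follow. No ventilation setting changes.
2. Replace the unused envelopes with centre-specific lists of randomly varying block sizes, prepared by someone outside recruitment. Do not disclose the sizes.
3. State who holds and opens the envelopes, and how the list used so far was divided between the centres.

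**What this buys.** Certain predictions fall from about 33% to 4% with sizes 2, 4 and 6, or from 8% if the present list is shared without exchange. Best guessing falls only to about 68–70% from 71%. In the shared, no-exchange layout it could even rise from its present 60%, because each recruiter would then see the whole of their own list; keeping the sizes undisclosed works against this. Later opening does not reduce predictability. It shortens the time for which the arm is known and limits losses after randomisation.

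**Cost.** A short amendment, new envelopes, readiness for either arm in the operating room, and a possible small final imbalance between arms. The article appeared about 10 months into a planned 18, so only the remaining patients benefit.

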### Selection of the participants

Patients with bladder cancer scheduled for open radical cystectomy and urinary diversion will be screened and recruited during routine perioperative assessment. Participants fulfilling the inclusion criteria will be asked for their signed informed consent. Withdrawal of consent may be initiated by the participant at any time during the trial.

Inclusion criteria are age over 18 years, patients with bladder cancer undergoing radical cystectomy and urinary diversion (ileal conduit or orthotopic bladder substitute) and provision of signed informed consent.

Exclusion criteria are age below 18 years, American Society of Anesthesiologists (ASA) physical status IV, history of severe chronic obstructive pulmonary disease (COPD, GOLD grades III or IV), history of severe or uncontrolled bronchial asthma, history of severe restrictive pulmonary disease, pulmonary metastases, history of any thoracic surgery, need for thoracic drainage before surgery, renal replacement therapy prior to surgery, congestive heart failure (NYHA grades III or IV), extreme obesity (Body Mass Index, BMI > 35 Kg/m^2^) and lack of patient’s consent.

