### Study endpoints

The primary outcome variables are PPC and PCT kinetics. PPC are defined as new infiltrates or atelectasis on a chest X-ray, abnormal breathing sounds on auscultation, respiratory failure defined as PaO_2_/FiO_2_ < 300 or the need for noninvasive or invasive ventilatory support within the first three postoperative days. PCT kinetics will be evaluated during and after surgery. Blood samples will be taken at 0, 2, 6, 12, 24, 48 and 72 h after surgical incision. According to recent data it is expected that PCT values will peak at approximately 24 h after surgery and that they should decline by approximately 50% daily in the case of an uneventful postoperative course. Therefore, in addition to the absolute values the change between T_0_–T_24_–T_48_ will also be evaluated [16, 22].

Secondary outcome variables are extrapulmonary complications: incidence of circulatory failure, gastrointestinal and renal dysfunction, hematologic and coagulation disorders and infection (Table 1).

**Table 1 Tab1:** Secondary endpoints

Endpoint	Time frame	Detailed description
Circulatory failure	28 days	Hypotension – MAP < 65 mmHg
		Severe cardiac arrhythmia – 40/min < HR > 150/min
		ScvO_2_ < 70%
		dCO_2_ > 7 mmHg
		Serum lactate > 2 mmol/L
		Severe metabolic acidosis (actual bicarbonate < 18 mmol/L)
		Acute coronary syndrome
		Acute left ventricular failure
		Pulmonary embolism
		Cardiac arrest
Gastrointestinal dysfunction	28 days	Constipation
		Ileus
		Anastomotic leakage
		Reoperation
		Disorders of liver function
Renal dysfunction	28 days	RIFLE criteria
Hematologic and coagulation disorders	28 days	Severe bleeding
		Coagulopathy – INR > 1.5
Infection	28 days	Any infection except from pneumonia

*MAP* mean arterial pressure, *HR* heart rate, *ScvO*
_*2*_ central venous oxygen saturation, *dCO*
_*2*_ central venous-to-arterial carbon dioxide gap, *INR* International Normalized Ratio

Tertiary endpoints are intensive care unit (ICU) days, in-hospital stay, in-hospital and 28-day mortality.

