### Duration of the trial

The annual number of open radical cystectomy and urinary diversion is around 100 in the two study centers. Recruitment of the participants is expected within 18 months. The final data collection and estimated completion date of the trial is March 2018.

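### PCT kinetics is a primary outcome, yet active infection is not an exclusion and the pre-randomisation PCT plays no part in eligibility: precision is at risk, though the arm comparison is not biased

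*Protocol article*

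**What the plan says.** Under Study endpoints, the protocol article states: "The primary outcome variables are PPC and PCT kinetics". The Background justifies PCT as a marker of the host inflammatory response, and the third objective is to relate the degree of inflammation to pulmonary and extrapulmonary complications.

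Selection of the participants prints the exclusion list in full. Besides age, ASA class, COPD and consent, it names "history of severe or uncontrolled bronchial asthma, history of severe restrictive pulmonary disease, pulmonary metastases, history of any thoracic surgery" and then "need for thoracic drainage before surgery, renal replacement therapy prior to surgery, congestive heart failure (NYHA grades III or IV), extreme obesity". Current infection, antibiotic treatment for infection and raised PCT do not appear there or elsewhere in the article.

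Under Preoperative assessment and admission, on the day before surgery, "a blood sample will be taken from included patients for baseline levels of PCT (T_0_), a chest X-ray will be performed". The next step is that "if there are no exclusion criteria, patients will be randomized into one of the study groups". The baseline PCT value is thus collected before allocation, but nothing depends on it.

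The Statistics section compares PCT between groups by two-way repeated-measures ANOVA, naming neither a transformation nor a baseline covariate, and relates PCT to organ dysfunction by Pearson correlation. Study endpoints adds that changes across T0, T24 and T48 will be examined alongside the absolute values. In Table 1 the infection endpoint, over 28 days, reads: "Any infection except from pneumonia".

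**The concern.** In a patient infected at admission, PCT reflects the infection and its treatment as well as surgery and ventilation. The protocol expects a peak near 24 h and then roughly a halving each day, but it ties that pattern to an uneventful course. With about 20 patients per arm, a handful of such patients can widen the PCT distribution, and they may well divide unevenly between arms.

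The third objective is exposed in a different way. The correlation of PCT with organ dysfunction is not a randomised comparison. Infection present before the intervention could raise both PCT and complications and produce an association unrelated to ventilation. Pearson correlation is also sensitive to a few extreme values.

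Eligibility belongs in the protocol, and the article gives its list in full, so this is a gap in a stated criterion and not a detail left to another document.

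**Working it through.** **The plan's own figures.** 10 blocks × 4 = 40 patients, 20 per arm at 1:1. No power, effect size, SD or infection rate accompanies the 40, so it cannot be derived from a power formula. For scale, 20 per arm gives 80% power at two-sided 0.05 for a standardised difference of (1.96 + 0.84) × √(2/20) ≈ 0.886. The protocol states 0.05; two-sided is assumed.

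**Chance imbalance.** Blocking on order of entry does not balance infection. With k infected among 40, split 20/20:
- k = 2: P(one each) = 20 × 20 / C(40,2) = 400/780 = 0.513, so P(both in one arm) = 0.487.
- k = 4: P(2:2) = C(20,2)² / C(40,4) = 36,100/91,390 = 0.395, so P(3:1 or worse) = 0.605.

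**Power at one time point.** Everything here is assumed, not taken from the documents: log-normal PCT, log-SD 0.8, true ratio 0.45, and infection raising PCT m = 5 or 10 times. The standardised log difference is ln(1/0.45)/0.8 = 0.998. With 20 per arm the noncentrality is 0.998 × √10 = 3.16, giving 87% power for a t test on log PCT. The raw-scale t test has about 75% by simulation (20,000 trials per scenario).

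Two models for an infected patient with surgical response Y:
- *Multiplies*: observed PCT = m × Y.
- *Adds*: observed PCT = Y + (m − 1) × B, where B is uninfected baseline PCT and the surgical peak is 5, 10 or 20 times B.

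| Model | Infected of 40 | Log-scale power, m = 5 / 10 | Raw-scale power, m = 5 / 10 |
|---|---|---|---|
| None infected | 0 | 87% | 75% |
| Multiplies | 2 | 80% / 73% | 53% / 27% |
| Multiplies | 4 | 75% / 64% | 41% / 18% |
| Adds, peak 10 × B | 2 | 86% / 84% | 76% / 73% |
| Adds, peak 10 × B | 4 | 85% / 81% | 74% / 70% |

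In the additive model the worst case (peak 5 × B, 4 infected, m = 10) is 74% log and 58% raw. With a peak of 20 × B, power stays at or above 84% log and 74% raw. Differences of a point are simulation error. With log-SD 1.0 and the multiplying model, log-scale power falls from 69% to 59%–52% with 4 infected.

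**Type I error.** A separate simulation (3,000 trials per scenario, log-SD 0.8, effect 0.9 SD, infection multiplying baseline and postoperative PCT alike by 3, 10 or 30) gave raw-scale rejection under the null of 0.001 to 0.042 with 2 to 6 infected patients. It is not inflated.

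**What baseline adjustment recovers.** In that same simulation, power for 3-, 10- and 30-fold elevation was:
- 2 infected: unadjusted log PCT 76%, 63%, 52%; log ANCOVA on baseline 75%, 68%, 67%.
- 4 infected: unadjusted 72%, 54%, 39%; ANCOVA 73%, 68%, 66%.

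With none infected, both give about 79–80%. Adjustment gains little at 3-fold elevation and recovers part of the loss at 10-fold or more.

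**The case against.** The strongest reply concerns size. The steep raw-scale losses appear only if infection multiplies the whole surgical response. Nothing in the documents supports that over an additive shift, under which the loss is often a few points. This stands, and a reader who infers that a few infected patients would swamp the ventilation effect goes further than the protocol allows.

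The number of infected patients is also a guess: patients are assessed with history and laboratory tests before this operation, and with none infected there is no effect. This stands too.

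The plan has some protection of its own. It looks at change from T0, which a single-time-point calculation does not represent. That mitigates the problem but does not remove it: absolute values are analysed as well, and a change score cancels infection only if its contribution stays constant through surgery and 72 h of antibiotics.

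A reader might infer systematic bias between arms. The documents do not support it, because T0 precedes random allocation; the split probabilities above hold for any unstratified characteristic carried by 2 or 4 patients.

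A reader might also infer that infections present at entry will be counted as events. The text introduces Table 1 as the incidence of complications, which ordinarily means new ones, so only the wording is loose.

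Finally, the Discussion calls the trial pragmatic, and an exclusion narrows the population. That is a real but small cost.

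**Conclusion.** The point holds in limited form. The eligibility criteria leave a primary outcome open to infection present before the intervention, and the baseline PCT that could help is collected but not used for eligibility or named as a covariate. The consequence for the arm comparison is lost precision and chance imbalance. For the third objective it is a possible distortion of the association between PCT and complications, whose size was not calculated.

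The power loss cannot be narrowed further from the documents. Under the stated assumptions it runs from negligible to serious, and it is much larger on the raw scale than on the log scale. What decides it is how many infected patients enter and whether infection adds to or multiplies the surgical PCT response; the protocol informs neither. The improvement is worth making because it is cheap, not because harm has been shown.

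**What to change.** 1. In Selection of the participants, add an exclusion for clinically active infection or therapeutic (non-prophylactic) antibiotic treatment at admission, defined by the investigators and checked before the allocation envelope is opened. A PCT cut-off is not needed for this: the documents offer no value for one, and they say only that the sample is taken, not that the result is back before allocation.
2. In Statistics, analyse log PCT adjusted for the T0 value. State that T0 is the sample from the day before surgery, since the objectives and endpoints sections place it at 0 h after incision.
3. In Table 1, state that infection counts only if new after surgery.

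Cost: a short amendment, with no new test. A few candidates are lost and the population is slightly narrower. The protocol says "The annual number of open radical cystectomy and urinary diversion is around 100 in the two study centers", so 18 months gives 100 × 1.5 = 150 candidates for 40 places, before other exclusions and refusals.
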